## Abstract

**Background:**

Older adults are underrepresented in suicide prevention research, even though suicide rates are higher in this age group (65+) than in any other age group in many countries worldwide. There are few clinical intervention studies that target this age group. A promising preventive intervention is the Attempted Suicide Short Intervention Program (ASSIP). Given differences in suicidal behaviour between older and younger adults, there is a need for suicide prevention intervention models that are adaptable to the heterogenic needs of older adults. This study protocol outlines the design of our upcoming study, which aims to evaluate a modified version of the Attempted Suicide Short Intervention Program (ASSIP) specifically adapted for older adults (65+), ASSIP for Older Adults (ASSIP-OA), as add-on to Treatment as Usual (TAU) and compared to TAU only.

**Methods:**

A multicentre two-group parallel randomised controlled trial will be conducted to compare TAU to ASSIP-OA (3–5 sessions) and standardized letters for 2 years as an add-on to treatment as usual. The trial, which is open labelled, will recruit 132 participants (65+) within psychiatric services in Sweden after a suicide attempt or hospitalisation for serious suicidal plans. The main modifications in comparison with the original ASSIP include (a) flexibility in treatment delivery (offering home visits, breaks and shorter/longer sessions as needed), (b) an additional session together with relatives or other support person(s), and (c) age-specific linguistic and content-wise adaptation of homework, letters, and case conceptualization. The primary outcome is a suicidal episode (fatal or non-fatal). Secondary outcomes include psychiatric symptoms, severity of suicidal ideation, coping style and quality of life. The trial also includes measures of feasibility, health-care utilization and negative effects of treatment.

**Discussion:**

This study has the potential to inform the development and implementation of a more person-centred care for suicidal older adults.

**Trial registration:**

ClinicalTrials.gov: NCT06831942. Registered February 21, 2025, revised May 21, 2025.

**Supplementary Information:**

The online version contains supplementary material available at 10.1186/s12888-025-07016-7.

## Background

Older adults are sorely underrepresented in suicide prevention research, despite the fact that suicide rates are higher in this age group (65+) than in any other age group in Sweden [1] and in many western countries worldwide [2]. There are few clinical preventive intervention studies that target this age group [3], and to the best of our knowledge there are to date no published studies set in Europe.

Older adult suicidal behaviour is a phenomenon involving complex processes of human behaviour that evolve over time, influenced by numerous factors, as opposed to a “normal” response to the aging process [4]. According to the Interpersonal Theory of Suicide in Older Adults [5] social disconnectedness is a main catalyst for the development of late-life suicidal ideation and behaviours. This concept includes feelings of burdensomeness, as well as thwarted belongingness. An effective model for suicide prevention in older adults must therefore go beyond the medical model which tends to see suicidal ideation and behaviour as symptoms of depression. A more systemic model is necessary to shift the focus to include preventive measures that can be taken by the suicidal individuals themselves, as well as other sources of potential support, including professional caregivers. An interview study conducted by our research group with older adults in geriatric psychiatry following a suicide attempt revealed that many participants had a limited understanding of their suicidal behaviour [6]. Furthermore, the results suggests that this lack of comprehension itself may pose a risk for future suicidal behaviour. A preventive intervention aimed at constructing a narrative around the suicidal phase could enhance understanding and help individuals regain a sense of control and agency.

In Sweden today, antidepressants and other types of psychoactive medication constitute the main treatment strategy available for older adults with depression and suicidal issues. While evidence-based therapies are available for younger adults with mental health issues, this is not the case for the oldest members of the population, despite the fact that their need for specialised services is at least as great [7]. In our recent interview study [6], older adult suicide attempters shared that age-related physical decline increased their dependence on the healthcare system. However, their psychological distress and life-weariness were often met with a lack of response from both primary care doctors and specialists. Some reported that their experiences with the healthcare system deepened their hopelessness, leading them to believe no help was available. In line with our focus group study with older adults with depression [8] older adults described frustration about the healthcare they received. They wanted to talk with professional caregivers about their depressions, about their suicidal feelings and their existential issues, and about what they themselves could do to improve their mental health. These experiences, taken together with results showing that many older adults attempt [9] and die by suicide [10] despite antidepressant treatment, speak to the need for evidence-based psychosocial interventions for older adults who are depressed and suicidal. The authors of a recent review on psychosocial interventions for suicidal older adults concluded that the international literature was so scanty that no conclusions could be drawn [11].

Suicidal behaviour in older adults differs from that in younger adults in several ways. While suicidal older adults tend to score lower on symptom rating scales than younger persons, their suicidal behaviour is characterised by greater intent and higher level of planning compared to younger adults [12]. Thus, many older adults die at their first suicide attempt [13]. A prevention program for older adults can therefore not be limited to actual suicide attempts, but rather must also target older adults with serious suicidal plans. In addition to mental ill health issues (often depression, alcohol use disorders or a combination), suicidality in older adults is more often associated with comorbid physical illness, functional limitations, and milder forms of cognitive dysfunction compared to their younger counterparts. Compromised executive function [14] and limited capacity for problem solving [15] have been observed in research involving suicidal older adults. Cognition is affected also in normal ageing, including the capacity to solve new problems and to reflect on new situations [16]. This includes those with mild cognitive impairment, who may require additional support when coping with age-related challenges. Given the differences in suicidal behaviour between older and younger adults, there is a need for suicide prevention intervention models that can be adapted to address the heterogenic needs of older adults.

A promising preventive intervention is the Attempted Suicide Short Intervention Program (ASSIP) [17]. The ASSIP model is based on the premise that individual behaviour is understandable through the lens of the person’s life history, individual vulnerability, life goals, and basic needs. The original ASSIP was developed in Switzerland where it has shown, as add-on to Treatment As Usual (TAU), an 80% decrease in risk of new suicide attempts within 24 months compared to ordinary treatment in a clinical cohort of adults (mean age 38 years) [17]. The ASSIP study is one of 53 studies included in a preprint meta-analysis on brief interventions following a suicide attempt [18]. The meta-analysis found evidence that brief interventions reduced the risk of suicide re-attempts compared to any control condition. In Sweden, ASSIP is currently being tested for individuals aged 18 and older [19], and early data are encouraging [20].

ASSIP is a short, structured clinical intervention in which the therapist and the patient collaborate to develop strategies that increase patient empowerment and thereby strengthen the patient’s ability to cope with future suicidal crises. The ASSIP model is mainly based on action theory, attachment theory and cognitive theory of suicidal behaviour, in which suicide is seen as a coping strategy (albeit dysfunctional) that a person may opt to use in an unbearable situation of mental pain, where no other coping strategies appear available [21]. Suicidal behaviour is thus seen as “goal-directed”, the goal being to end mental pain [22]. The positive results of the Swiss ASSIP trial [17], appears to at least in part be related to improved coping strategies. Reduced dysfunctional coping, as well as greater problem- focused coping were observed in participants who took part in the ASSIP intervention. Further, ASSIP participants score higher on self-distraction (12 months) and lower on self-blame (24 months) compared to participants who received ordinary treatment [23]. The collaborative approach in ASSIP, the direct focus on suicidal behaviour, and the emphasis on developing strategies to enhance patient empowerment and coping skills from a lifespan perspective appears to align with the needs expressed by older adults [6, 24]. However, further emphasis on engaging social support including support from professional caregivers [25], may be beneficial in counteracting social disconnectedness, a salient feature of suicidal behaviour in older age groups [26, 27].

In its original form, ASSIP is a 3–4 session intervention, an add-on to usual treatment, which is initiated shortly after a suicide attempt [21]. The ASSIP therapist encourages patient to share their own personal history, putting a spotlight on the patient’s narrative regarding their suicide attempt, including events and emotions. This first session is video-recorded and played back at the second session, as the patient, and the therapist sit side-by-side and watch the film, identifying triggers, warning signs, and the participant’s suicidal mode including automatic thoughts, emotions and bodily reactions that were experienced during the suicidal crisis. This can be used to replace dysfunctional coping strategies with more functional ones, to hinder the development of the suicidal mode in the future. The aim is the identification of biographical vulnerabilities associated with suicidal behaviour, and to jointly develop long-term therapy goals that need to be shared with the longer-term health care network (e.g. psychotherapists, mental health professionals, GPs, caregivers, etc.). Homework is completed after the first session. It is psychoeducational in nature; participants make notes to ensure that the description of events in the homework text is in line with their own experiences. At the third session, the patient and the therapist revise the patients personal case conceptualisation of the suicidal behaviour, a summary of biographical vulnerabilities, individual triggering events, and suicidal process, as well as relevant therapy goals and warning signs (long-term and acute). Safety strategies are formulated and compiled into a list on an easily accessible card, including individual and social strategies to distract from suicidal crises and to ensure a safe environment and phone numbers for easy access to relevant care services, helplines, and supportive friends/relatives as chosen by the participant. A fourth session is optional, when there is a need for repetition and practicing of the strategies. A 2-year outreach component follows, during which participants are sent semi-standardised letters (signed by the therapist) to help them remember to use the strategies learned during the ASSIP sessions and to let them know that they can contact the therapist should need arise, and to provide easy access to health care system. If a new suicidal crisis emerges, the ASSIP therapist offers a “booster” session to go through the case conceptualisation again and the safety plan is updated.

There is a real need for fully powered studies of brief preventive interventions for older adults after non-fatal suicidal acts and older adults hospitalised for suicidal prevention. Drawing from the promising results of ASSIP in adults we will now conduct a randomised controlled trial (RCT) to evaluate a modification of ASSIP specifically designed to meet the needs of suicidal persons aged 65 and above, the ASSIP-Older Adult program (ASSIP-OA).

## Objectives and hypothesis

This paper outlines the study protocol for our upcoming study, which aims to evaluate a modified version of the Attempted Suicide Short Intervention Program (ASSIP), specifically for older adults (65+), the ASSIP for older adults (ASSIP-OA), as an add-on to usual treatment. The efficacy of the ASSIP-OA intervention will be evaluated by comparing it to a control group receiving only treatment as usual (TAU).

The main hypothesis is that participants randomised to the add-on treatment condition - the ASSIP-OA intervention - will experience a preventive effect on suicide and suicide attempts within 6, 12, and 24 months following the index episode. Also, we anticipate participants in the experimental condition to show better improvement in psychiatric symptoms/severity of suicidal ideation/coping skills/quality of life (secondary outcomes). Additionally, we aim to investigate if the brief preventive intervention (ASSIP-OA) is feasible, based on its acceptability, appropriateness, deliverability and fidelity, and whether participants have fewer days of inpatient care or experience any negative side effects. Further, the study also includes a qualitative approach to explore what kind of challenges and opportunities (a) older adults and (b) ASSIP-OA therapists experience in relation to implementing the brief preventive intervention, and if the modifications that we made in ASSIP-OA are relevant for older adults.

## Methods

### Study setting and design

This study is designed as a multicentre two-group parallel randomised controlled trial (RCT), to be conducted within psychiatric services in the Swedish regions of Västra Götaland, Skåne, and Halland. Several additional regions have shown interest and may be added. Participants are randomly assigned to either:

a brief 3–5 session preventive intervention (approx. 1 session per week), the Attempted Suicide Short Intervention Program for Older Adults (ASSIP-OA), which is an add-on to usual treatment.a control group receiving treatment as usual (TAU) only.

Measurements will be taken prior to randomisation and after the last session (or after 5 weeks for the control group) and follow-up measurements (see below) will be assessed at 6, 12 and 24 months after the last session. An overview of data to be collected at the various timepoints is shown in Fig. 1. Following the baseline measurement, randomisation will take place electronically via REDCap (Research Electronic Data Capture) [28] and will be conducted using block randomisation with varying block sizes and with an allocation ratio of 1:1 between intervention groups. The randomisation procedure was designed by a statistician at the University of Gothenburg, independent of the research group. Randomisation will be blinded to the data processors, as well as to the researchers and clinicians conducting the initial assessments and screening (prior to randomisation). The size of the randomisation blocks will remain undisclosed. Due to the design of the intervention, blinding participants to their assigned group will not be possible. As it is anticipated that usual treatment will vary somewhat between the study locations, it will be mapped for each patient. Data on clinical diagnoses, healthcare contacts and treatments for mental health concerns during 24 months before and after baseline measurements are derived from medical records.

The study will follow the CONSORT guidelines and was pre-registered at Clinical Trial.gov NCT06831942 on February 21, 2025 and revised May 21, 2025. The present study protocol follows the recommendations for clinical trial protocols from the SPIRIT Declaration [29, 30], see Supplementary material 1 for checklist.

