### Participants and recruitment

Participants are recruited from psychiatric healthcare settings at participating centres, including inpatient psychiatric wards, outpatient psychiatric services, emergency care, and medical wards via consultation liaison services. Patients (65+) who have been hospitalised (minimum 1 night) in connection with a suicide attempt during the last 3 months or an episode of serious suicidal planning during the last month at any of the participating clinics are eligible for participation in the study. Unit managers, doctors and medical staff working in the inpatient wards, outpatient clinics and consultation psychiatric services will be informed about the study and asked to identify potential participants and provide interested patients with oral and written information about the trial.

Individuals who meet the eligibility criteria (see below) are invited to a brief screening to confirm their suitability for the study. If they remain eligible and wish to receive more information, the staff will provide detailed study information, which participants can review at their own pace. They will also have the opportunity to ask questions, which can be addressed by the study researcher as needed. The study researcher will then contact the patient to discuss the research details and answer any remaining questions. If the patient chooses to enrol, they will sign the consent form, and baseline measurements will begin. After the baseline assessment, the participant is randomised to either the intervention group (ASSIP OA + TAU) or the control group (TAU). Participants receive information about allocation in connection with the baseline visit, along with information about their scheduled appointment with an ASSIP-OA therapist or their next scheduled research assessment.

All quantitative data will be securely stored in REDCap and presented at the group level to ensure anonymity.

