### Sample size

A total of 132 participants will be included in the trial. The power calculation, i.e., the number of participants needed in each intervention group, is based on the previous ASSIP study of [name] and colleagues [17]. In that study, 26.7% of the participants in the control group, usual treatment, and 8.3% in their intervention group, ASSIP, reattempted suicide during follow-up. Based on clinical experience as well as prospective data from our previous multicentre study [12] for persons 65 + receiving usual treatment, we choose to calculate power based on an expected repetition risk of 30% in our control group (usual treatment), and 10% in our intervention group receiving ASSIP-OA plus TAU. Furthermore, given a desired power of 0.80 (a 4/5 chance of discovering an effect if it exists, regarded as adequate in this context) and a risk level of 5%, 60 participants in each condition is needed. We further expect a dropout rate of 10%, thus each group will therefore comprise 66 participants.

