### Outcome measures

#### Primary outcome

The primary outcome variable at 6-, 12- and 24-month follow-up is any “new suicidal episode,” a composite rating that is coded “yes” in the event of (a) a new suicide attempt as registered in the participant’s medical record or the national hospital register or (b) suicide death as registered in the national cause of death register.

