### Data analysis

We will use an intention-to-treat analysis. The primary outcome will be analysed using chi-square analyses. The secondary outcomes will be analysed using a so-called “mixed effect model approach” with the aim of examining changes before and after treatment as well as during the follow-ups. This approach can take into account data clustering and covariates as well as possible dropouts.

We will examine effects both between and within groups, to be able to determine if the preventive intervention ASSIP-OA in addition to TAU has a better effect than the control group, treatment as usual (TAU), after the intervention (between-group effect). Further, we want to find out whether ASSIP-OA and the control group have improved over time (within-group effect) and, if the ASSIP-OA has any effect, whether such effect is “driven” by the ASSIP-OA (interaction effect). The statistical approach is based on regression analyses. Contrary to more traditional variable-oriented analyses for repeated measurements, it has the benefit of taking into consideration the fact that data are not independent at repeated measurements over time and provides better handling of missing data by incorporating all available information. This method is now regarded as preferable to using more traditional methods for missing data in clinical studies.

For qualitative data collected through individual and focus group interviews, transcribed interviews will be analysed, and themes and subthemes will be identified and categorised following Braun and Clarke’s thematic analysis [51].

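### The stated primary test is an unadjusted chi-square that uses neither index event nor region, so it cannot correct a chance imbalance on either

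*Protocol article*

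**What the plan says.** Participants and recruitment admits two index events. Patients aged 65 or over qualify after a hospital stay of at least one night "in connection with a suicide attempt during the last 3 months or an episode of serious suicidal planning during the last month". The Discussion presents the second group as a deliberate extension of the original programme.

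Study setting and design names three regions and adds: "Several additional regions have shown interest and may be added". On the comparator it says: "As it is anticipated that usual treatment will vary somewhat between the study locations, it will be mapped for each patient". Randomisation is electronic and "will be conducted using block randomisation with varying block sizes and with an allocation ratio of 1:1 between intervention groups". An independent statistician designed it and block sizes are withheld. No stratification factor is mentioned, and none is ruled out.

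Data analysis states: "The primary outcome will be analysed using chi-square analyses". The secondary outcomes get a mixed-effects model, and the remark "This approach can take into account data clustering and covariates as well as possible dropouts" refers to that model only.

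**The concern.** The endpoint is a new attempt or a suicide death. Sample size bases its rates on re-attempts in the earlier ASSIP trial and on the group's own prospective data, and speaks of an "expected repetition risk of 30% in our control group (usual treatment), and 10% in our intervention group receiving ASSIP-OA plus TAU". A patient whose index event was a plan may have no attempt to repeat, so equal risk in the two index groups cannot be taken for granted. Index event is a plausible prognostic factor. Region is another, because usual care is expected to differ by location.

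Index event is established at screening with the short C-SSRS, and region is known at enrolment. Both are available before allocation. A trial gets one randomisation. If the arms happen to differ on a prognostic factor, a crude chi-square carries the difference into the estimate, while a stratified or adjusted analysis removes it.

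**Working it through.** **Inputs from the article.** Sample size: 30% versus 10%, power 0.80, 5% risk level (two-sided assumed), 60 per arm, 66 per arm after dropout. Data analysis: chi-square.

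**Inputs not in the article, assumed with a range.** Attempter share *s* from 30% to 70%; attempter to plan-only risk ratio *r* from 1 to 3; overall control risk held at 30%.

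**1. The plan's own figure.** Pooled variance: [1.96√(2 × 0.20 × 0.80) + 0.842√(0.30 × 0.70 + 0.10 × 0.90)]² / 0.20² = 61.6, so 62 per arm. Unpooled variance gives 58.9 (59) and the arcsine method 59.01 (60). The stated 60 is reproduced. Expected events: 66 × 0.30 + 66 × 0.10 = 26.4.

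**2. Chance imbalance if allocation is not stratified.** With *n* per arm, the number of attempters in one arm is hypergeometric, and the SD of the between-arm difference in share is (2/n)√[n s(1 − s) n/(2n − 1)].
- *n* = 66, *s* = 0.5: √(66 × 0.25 × 66/131) = 2.88, and 2 × 2.88/66 = 8.7 points.
- Possible differences move in steps of 2/66 = 3.03 points, so 10 or more means at least 12.1. Probability 0.22; at a share of 30% or 70%, 0.18.
- At least 15 points: 9–12%.
- At 60 per arm the SD is 8.4–9.2 points, with 32–36% for 10 or more and 7–10% for 15 or more. The higher first figure arises largely because exactly 10 points (3 × 2/60) is attainable there.

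**3. Shift in the crude risk difference.** Plan-only risk = 0.30/(s r + 1 − s); attempter risk = *r* times that; *g* is the gap. With no treatment effect, an imbalance *d* shifts the difference by *d* × *g*. For *d* = 10 points:

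| Risk ratio | s = 30% | s = 50% | s = 70% |
|---|---|---|---|
| 1 | 0 | 0 | 0 |
| 2 | 2.3 | 2.0 | 1.8 |
| 3 | 3.8 | 3.0 | 2.5 |

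Under the planned effect, with both groups' risk cut to one third, the shift is (d/2)g + (d/2)(g/3) = (2/3)dg. That is 1.2–1.5 points at ratio 2 and 1.7–2.5 at ratio 3. The standard error of the planned difference is √[(0.21 + 0.09)/66] = 6.7 points.

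**4. Operating characteristics.** Simulation, 300,000 trials per scenario, 60 per arm, chi-square against a Mantel-Haenszel (MH) test stratified by index event. Ranges are over *s*.

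| Risk ratio | Chi-square type I, all | Chi-square type I, imbalance ≥15 points | MH type I, imbalance ≥15 points | Power, chi-square | Power, MH | Power, MH with stratified allocation |
|---|---|---|---|---|---|---|
| 1 | 0.052–0.053 | 0.050–0.053 | 0.048–0.051 | 0.80 | 0.80 | 0.80 |
| 2 | 0.052–0.054 | 0.068–0.078 | 0.049–0.051 | 0.80 | 0.81 | 0.81–0.82 |
| 3 | 0.052–0.053 | 0.084–0.120 | 0.049–0.050 | 0.80 | 0.82–0.83 | 0.82–0.84 |

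If allocation is stratified by index event but the test stays crude, type I error falls to 0.046–0.048 (ratio 2) and 0.037–0.046 (ratio 3). The chi-square then becomes conservative.

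**5. Region.** The article gives no region sizes or regional risks, so this part cannot be sized.

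**The case against.** The planned test is sound. Chance imbalance is part of the variation that a chi-square after randomisation already reflects, and the simulation confirms this: about 5% type I error and 80% power over all randomisations, whatever the prognostic strength. A shift of 1.2–2.5 points under the planned effect is only 0.2–0.4 of its standard error. All of that stands.

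Four stronger readings are tempting, and the article supports none of them.
- **That randomisation is unstratified.** The article is silent, and it condenses a fuller document that is not shown. The list may already be stratified by centre.
- **That index event is a main driver of re-attempt.** No risk by index event is given. The Background and Discussion justify enrolling patients with plans because many older adults die at a first attempt, so they are not presented as low-risk. With equal risk the shift is zero.
- **That the result is biased.** It is not biased on average; the harm is conditional on the imbalance drawn.
- **That a small or late-added region could end up mostly in one arm.** Without region sizes this is speculation. Both arms receive usual treatment, and the variation is expected to be modest.

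What the objection does not remove is the named analysis. The article assigns the primary outcome a test that cannot adjust, and mentions covariates and clustering only for the secondary outcomes. This matters even if allocation is stratified, since the crude test would then ignore the strata.

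**Conclusion.** The point holds as a moderate weakness in robustness and efficiency, and does not make the test invalid. The stated primary analysis ignores two factors known before randomisation, in a trial with about 26 expected events.

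If index event carries two to three times the risk, an imbalance of 15 points or more (7–10% of unstratified randomisations at 60 per arm) raises the chi-square's type I error to between 0.07 and 0.12, while the stratified test stays near 0.05. Averaged over randomisations, stratified allocation with a stratified test gains about 1 to 4 power points at those ratios. If index event is not prognostic, essentially nothing is gained or lost.

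These sizes rest on the assumed attempter share and risk ratio, and the imbalance figures also on allocation not being stratified by index event.

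**What to change.** Before outcome data are seen, pre-specify a primary analysis of the binary outcome adjusted for index event (attempt versus plan only) and for region, with sparse regions merged by a rule set in advance. A Mantel-Haenszel test, or logistic regression reporting a marginal risk difference, would serve. Keep the chi-square as supportive. A log-rank or Cox analysis is not needed for this purpose and would turn a fixed-time binary endpoint into a time-to-event one.

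State whether allocation is stratified, and by what. If it is not, stratify later enrolments in REDCap by index event, and by region where numbers allow.

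No new data and no larger sample are needed. The cost is a small amendment, a new allocation table if one is required, and some sparse strata: three regions by two index events make six cells, or 26.4/6 = 4.4 expected events per cell on average. Added regions would thin these further, hence the merging rule.
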